## Methods

This study has been designed as a parallel RCT with two equal-sized groups (see Fig. 1). We used the SPIRIT reporting guidelines; please see the Additional file 1 for the SPIRIT checklist [77]. Figure 1 outlines the study protocol procedure and Table 1 provides the study timeline, as per SPIRIT guidelines [77]. Participants will be randomized to the add-on nurse practitioner-led care (NP-led care arm) as the intervention arm of the study over a 6-month period vs their usual medical care comprising the control arm (usual care arm), consisting of their community neurologist and/or family physician and registered nurse (RN). Usual care will vary amongst community neurologists’ practice, but typically involves annual visit.

**Fig. 1 Fig1:**
[figure not shown]
Study protocol procedure and flow

**Table 1 Tab1:** Study timeline

Timepoint	T_**1**_	T_**2**_	T_**3**_	T_**4**_	T_**5**_	T_**6**_	T_**7**_	T_**8**_	T_**9**_
Enrollment	X	X							
Eligibility screen - EQ5D	X	X							
Informed consent	X	X							
Allocation		X							
Baseline questionnaires - HADS - MFIS - EQ5D - CAREQOL- MS			X						
3-month follow-up questionnaires - HADS - MFIS - EQ5D - CAREQOL- MS				X					
6-month follow-up questionnaires - HADS - MFIS - EQ5D - CAREQOL- MS - CSQ					X				
12-month follow-up questionnaires - HADS - MFIS - EQ5D - CAREQOL-MS						X			
Quality assurance							X		
Data analysis								X	
Results									X

*****Timepoints in 3-month increments; see Abbreviations for list of validated questionnaires provided at baseline, 3-month, 6-month, and 12-month follow-ups

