### Data collection

Participants may withdraw from the study at any time without effect to their care. They will be informed they will not receive any incentive for participation and the risks are not beyond the day-to-day risks. After the participants have provided informed consent, they will be invited to complete the questionnaires. PwMS will be asked to complete the Hospital Anxiety and Depression Scale (HADS) [74], Euro Quality of Life Measurement (EQ5D) [23], Modified Fatigue Impact Scale (MSIF) [81, 82], at specific timepoints (baseline, 3 months, 6 months, and 12 months); their caregivers (where applicable) will be asked to complete the Caregiver Health-Related Quality of Life in MS (CAREQOL-MS) questionnaire at the same timepoints [83]. These questionnaires will take approximately 10 to 15 min to complete at each time point. Participants will be asked to keep a participant diary submitted at the same time points, recording the number of outpatient visits and phone calls to their neurologists, family physicians, registered nurses, pharmacists, physiotherapists, occupational therapists, and other allied health professionals (such as massage therapists, chiropractors, dieticians). Alberta has a linked provincial system where all emergency visits and inpatient admissions are recorded. This database will be searched for any emergency visits and inpatient admissions for the 6-month period that the participants are involved in the study.

Participants’ satisfaction with the level of care provided to them will be measured at 6 months at the conclusion of their NP care using the validated Consultant Satisfaction Questionnaire (CSQ) [73, 84]. The CSQ consists of 18 Likert scale questions, ranging from 1 = strongly disagree to 5 = strongly agree, with the higher score indicating a higher level of patient satisfaction.

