### Randomization, allocation, and blinding

This is an interventional study with parallel groups, done through block randomization (variable block sizes) 1:1, using centralized secure website to (1) intervention group (NP-led care) and (2) control group (usual care—community neurologist/family physician and registered nurse (RN), in a non-inferiority framework). The EPICORE Centre will randomize and allocate consented patients who meet eligibility inclusion and exclusion criteria on a 1:1 ratio using a centralized secure website. Block randomization (using variable block sizes) will be used to ensure there are equal participants in the intervention and control arms and to further conceal allocation. The randomization sequence was generated using R blockrand (https://cran.r-project.org/package = blockrand) and the randomization function of REDCap (REDCap Consortium, Vanderbuilt University, Nashville, TN, USA). Participants will be enrolled into the study by the community neurologist’s office (e.g. registered nurse, NP, or neurologist). Participants will register themselves through filling out an iPad questionnaire in the waiting room of community neurologists’ offices, indicating whether they wish to participate in the study or not. The participants, after providing informed consent, will be randomized by the independent EPICORE Centre’s research team to either the intervention group of NP-led care or the control group of standard care provided by community neurologist and registered nurse. After participants have provided informed consent, the EPICORE Centre’s research team will use a centralized website to randomize the patients to either the intervention or control group and then the NP and/or community neurologist will provide the intervention. Participants will be randomized to either the intervention group of NP-led care or the control group of standard care provided by community neurologist and registered nurse. Due to the nature of the intervention, blinding of the providers or patients will not be possible. However, the statistician will be blinded as to which group represents the intervention and control.

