### Intervention arm (NP-led care arm)

Participants randomized to the intervention group will be contacted by the NP to be scheduled for an appointment with the NP within 4 to 6 weeks from the date of the referral. The NP consultation will include patient history, physical examination, symptomatic management strategies as appropriate (e.g. bladder and bowel management strategies, fatigue management, depression, anxiety, spasticity), discussion of mental and physical health resources for symptomatic treatment, support, physical and mental health resources to optimize functioning (e.g. home care or physical/occupational therapy referral), and quality of life interventions. The NP will follow up with the patient either in person, by phone, or by videoconferencing at 3 months, at 6 months, and again at 12 months. The NP will be accessing the electronic medical record offered by Alberta Health Services [85] to maintain charting consistency in diagnostic testing, appointments, and communications [85]. During the visits, the NP will check the completion of study questionnaires at the appropriate timepoints, and ask the participant +/− caregiver about the completion of questionnaires. If the NP feels that he/she needs help in managing a participant, he/she will refer the participant back to the community neurologist and/or family physician in charge of the participant at any time throughout the study. As mentioned above, the NP will be sending summaries of visits to the neurologists and family physicians and may ask questions of the community neurologists as to their preferences in treatment approaches as needed (e.g. disease-modifying therapies, treatment of relapses with steroids) in individual situations. This fits within the multidisciplinary model of MS care, seen in MS clinics [11].

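### Table 1 puts the self-reported baseline HADS after allocation in an unblinded trial, so knowledge of the arm may affect the baseline used in the primary change score

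*Protocol article*

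**What the plan says.** In Table 1 (Study timeline), enrolment, eligibility screening with the EQ5D, and consent are marked at T1 and T2. Allocation is marked only at T2. The row "Baseline questionnaires - HADS - MFIS - EQ5D - CAREQOL- MS" is marked only at T3, and the 3-month questionnaires at T4. The footnote reads "Timepoints in 3-month increments".

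The text gives no different order:
- Data collection: "After the participants have provided informed consent, they will be invited to complete the questionnaires".
- Randomization, allocation, and blinding: "After participants have provided informed consent, the EPICORE Centre’s research team will use a centralized website to randomize the patients". Consent and eligibility are the only stated conditions.
- Recruitment: the one questionnaire placed ahead of randomization is the EQ5D on the waiting-room iPad.
- Blinding: "Due to the nature of the intervention, blinding of the providers or patients will not be possible".
- Intervention arm: after randomization the NP contacts the patient to book a visit "within 4 to 6 weeks from the date of the referral". Under Control arm, the NP contacts patients to book a deferred visit.

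Under Outcomes and Statistical analysis, the primary outcome is the between-group difference in change in HADS-D and HADS-A from baseline to 3 months, tested by independent t-test. The Population section relies on this baseline when it describes participants as their own controls.

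**The concern.** Randomization makes the arms comparable up to the moment of allocation. A measurement taken after that moment, by people who know their arm, no longer has that protection. HADS asks patients to rate their own anxiety and depression, and learning that specialist nursing support is coming soon, or only after the study, could plausibly change the answers.

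Because the primary analysis subtracts this baseline, a between-arm difference caused by the allocation passes into the estimated effect. Adjusting for baseline instead of subtracting it would not remove the problem, because the covariate itself would be measured after randomization.

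The first NP contact raises the same question. The abstract gives the intervention arm a baseline visit with the NP, and the Intervention arm section has the NP check questionnaire completion during visits. The text does not say that baseline HADS is complete before then.

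**Working it through.** **Order of events.** Table 1: allocation T2, baseline T3. Data collection: questionnaires after consent. Randomization section: randomization after consent. The two text statements share the same starting point and do not rank questionnaires against randomization. Table 1 is the only place in the material shown that does.

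**Effect on the contrast.** Let b be the between-arm difference (NP minus control) in baseline HADS caused by knowing the allocation. Let c be the part of it still present at 3 months, and θ the effect of care.

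Expected difference in change = θ + c − b.

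- Shift gone by 3 months (c = 0): bias = −b.
- Shift fully persistent (c = b): bias = 0.
- Relief in the NP arm or disappointment in controls makes b negative, so a transient shift adds a positive amount and understates an NP benefit. The opposite reaction would overstate it.

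**Scale: the plan's own figure.** The sample size section gives a difference of 1.5, 80% power, two-sided alpha 0.05 and 100 per group. It prints no SD, so 200 cannot be reproduced from printed inputs alone. Back-solving: SD = 1.5 / [(1.960 + 0.842) × √(2/100)] = 3.79. SDs of 3.75, 3.78 and 3.80 return totals of 198, 200 and 202. I use 3.78 as an assumed change-score SD. Then SE = 3.78 × √(2/100) = 0.535.

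**Illustration.** The sizes are assumed and the shift is taken as wholly transient (c = 0). Type I error is two-sided with θ = 0: 1 − Φ(1.96 − b/SE) + Φ(−1.96 − b/SE), with b as an absolute value. Power is for a true 1.5-point benefit when the bias works against the NP: Φ((1.5 − b)/SE − 1.96).

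| Absolute b (assumed) | Share of 1.5 | Type I error | Power if against NP |
|---|---|---|---|
| 0 | 0% | 5% | 80% |
| 0.25 | 17% | 7.5% | 65% |
| 0.50 | 33% | 15.5% | 46% |
| 0.75 | 50% | 28.9% | 29% |

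The extra type I error lies almost wholly in the direction of the bias. Under relief or disappointment those rejections would wrongly disfavour the NP.

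**Baseline adjustment.** With a pre-post correlation ρ (assumed) and c = 0, ANCOVA leaves a bias of size ρ × b. For b = 0.5 that is 0.25 at ρ = 0.5 (type I error 8.4%) and 0.35 at ρ = 0.7 (15.0%), taking 3.78 as the cross-sectional SD.

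**The case against.** **Table 1 is partly schematic.** T5 (6 months) and T6 (12 months) are adjacent, and the last three columns are quality assurance, analysis and results, so the 3-month spacing cannot be literal. Figure 1, which is captioned as the procedure and flow, is not visible here. This stands. A reader might infer that baseline was taken three months after allocation, or after the first NP visit, and the document supports neither. It does not, however, reverse the T2 to T3 order.

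**The text leaves room for the opposite order.** Signed consent goes to the study team, who check eligibility before randomizing, so questionnaires could be completed in that interval. The EPICORE Centre also sends the surveys directly to participants and issues its own baseline reminder, which partly separates baseline collection from NP visits. This stands as a possibility. It is not a requirement, and the table says otherwise.

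**No harm is shown.** A reader might infer that patients did rate their mood knowing their arm, or that the design manufactures a benefit for the NP. Neither follows. The document does not say when participants learn their allocation, every value of b above is assumed, a persistent shift cancels, and the most natural reaction would bias against the NP. This limits the point to an exposure to bias.

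**Conclusion.** The point holds as an exposure to bias in the primary contrast. As printed, the plan takes baseline HADS after allocation in an unblinded trial, and the text shown has no rule placing it before randomization or first NP contact. That a shift occurred, how large it was and which way it went are all unknown.

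If a shift occurred and had gone by 3 months, the bias equals its size with opposite sign. Half a point would be one third of the target difference. A shift that only partly persists gives a proportionately smaller bias. The error rates and power figures rest on the back-solved SD of about 3.79, on 100 per arm, and on full disappearance of the shift by 3 months. The sample size is unaffected.

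**What to change.** **The rule.** State that randomization is released only once the patient's baseline HADS has been submitted, and correct Table 1 accordingly. The caregiver questionnaire need not hold up randomization: caregivers are approached after the patient enrols and consent separately.

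**For this trial.** The Trial status section says recruitment is complete, so a form-order rule cannot help those already enrolled, and Table 1 must describe what was done. Before the final analysis:
1. State the order actually used. If baseline HADS did precede randomization, correcting Table 1 and saying so settles the point on allocation.
2. Tabulate, by arm, baseline completion dates against allocation and first NP contact.
3. If any baselines followed allocation, prespecify a sensitivity comparison of 3-month HADS between arms that does not use the post-allocation baseline. Adjust for the screening EQ5D only where it was retained: the text describes it for the iPad route and not for family-physician referrals.
4. Add an analysis restricted to baselines completed before allocation, if any exist.

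**Cost.** A table edit, a date listing and one or two extra analyses. The unadjusted 3-month comparison is less precise than the change score when ρ exceeds 0.5: at an assumed ρ of 0.7 and a cross-sectional SD of 3.78, the change-score SE is 3.78 × √(2 × 0.3) × √(2/100) = 0.41, against 0.535. It also leaves a persistent shift in the estimate, which the change score would cancel, so the two results should be read together.

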### Study setting

The RCT will be conducted in a distributed, outreach model, in the offices of seven community neurologists who follow PwMS as a part of their general neurology private practices, with the NP based in the multidisciplinary, tertiary MS clinic at the University of Alberta Hospital, Canada. The NP will provide outreach support to the community neurologists’ offices, seeing patients within their private office settings, based on referral from the community neurologists. Family physicians will be able to refer their PwMS directly to the NP, if they are not followed by any neurologist, through the already established MS clinic referral process.

### Population (inclusion/exclusion criteria)

All adult PwMS who are thought to potentially benefit from NP involvement in their care will be referred to the NP by community neurologists or family physicians and assessed for eligibility and informed consent. Informal caregivers (defined as a partner or close friend who provides for, and/or supports the PwMS) will also be approached to participate in the study. Informal caregivers for PwMS as defined above will be approached to be involved in the study, after the PwMS they care for enrolls in the study and nominates for the inclusion of their caregiver into the study. Consent will be obtained by the software application the PwMS uses to access the study; this will be followed up by the NP and/or neurologist on the first visit.

Inclusion criteria for the study includes:
≥ 18 years of age,Diagnosed with MS as per the clinical 2010 McDonald criteria [78],Followed by a private-practice general neurologist and/or family physician,Willing to provide informed consent,Have the ability to complete questionnaires on their own or with assistance (either by computer or paper copy),Be able to attend outpatient visits with the NP,English-speaking, andWho are experiencing disability from their MS with an Expanded Disability Status Scale (EDSS) between 3.0 and 8.5 or a Patient Determined Disease Steps (PDSS) ≥ 2 [79, 80].

Exclusion criteria for the study are as follows:
People without a diagnosis of MS as per the clinical 2010 McDonald criteria [78],Younger than 18 years of age,Have an EDSS of less than 3.0 or PDDS less than 2,Have a diagnosis of a central nervous system inflammatory disorder other than MS,Are unable to provide informed consent,Are unable to attend visits with the NP in person, or by telehealth.

PwMS will be included at baseline irrespective of whether they have depression at study entry, or long-term depression, or depression already managed with pharmacotherapy or therapies. This is because of studies suggesting that PwMS scoring high on depression levels often have not been previously identified as having depression or anxiety within a cohort [28], and that even those with previously identified depression or anxiety are often undertreated [45]. Baseline testing will be done for all participants; therefore, participants will become their own controls, as to outcomes on change in levels of depression and anxiety over 3 months, and then 6 months in addition to other quality of life outcomes. Therefore, we will see if the NP involvement and the consequent additional supports, counseling, etc., provides a change over time from baseline depression and anxiety levels. We postulate that depression and anxiety may be most responsive to the holistic approach of an NP over the short term in comparison with other quality of life measures [30, 47]. The primary outcome of depression and anxiety score changes at 3 months was chosen as the primary outcome due to published studies examining efficacy of interventions for depression and anxiety for PwMS carrying out active intervention strategies ranging in duration from 6 to 16 weeks (median 12 weeks), demonstrating overall efficacy in mainly depression and suggested efficacy in anxiety by a systematic review and meta-analysis [47].

### Recruitment

Recruitment will be conducted using two methods, as participants will be recruited from various community neurologists’ offices and family physicians’ practices in Northern Alberta. There are seven community neurologists who have volunteered to participate in recruiting of PwMS through their practices and iPads will be placed in their office waiting rooms in addition to flyers. The neurologists will mention the study to their patients. If a PwMS expresses interest in participating in the study, they will be given a flyer and/or, based on personal preference, an iPad containing the study information will be provided to them and the patients will be placed out in the waiting room to complete the recruitment back in the waiting room after the neurologist office visit, at their discretion. Therefore, the neurologists will not know if their patients have decided to participate or not, until they have received a communication from the NP. There is also a QR link, on the paper flyer and on the iPad, that allows the potential participant to take the study information home with them to consider. Potential participants using the iPad will complete the EQ5D questionnaire and are then given an interpretation of their score. The iPad EQ5D scoring with consequent link to the study outline/explanation and consent has been developed by the EPICORE Centre team. They will be encouraged to reach out to their neurologist to discuss their score with their neurologist as a part of the introduction and invited to self-register for the study if they indicated they would be interested in potentially exploring alternate ways of healthcare delivery to optimize their health and MS management. If the patient opts to self-register, they will be provided with the participant information sheet on the iPad and invited to complete the informed consent form. The signed informed consent form will be electronically sent to the study team where they will assess the patient with the eligibility inclusion/exclusion criteria. Those who meet the eligibility criteria will be randomized to the intervention or control arms as per this study protocol.

Those PwMS who are followed primarily by a family physician, outside of a neurologist, can be referred by their family physician directly to the NP via the established tertiary MS clinic fax system. These referrals will be screened by the NP and one of the researchers (PS, a MS specialist neurologist). Those who meet the eligibility inclusion criteria will be invited to take part in the study. If the patient consents to the study, they will be randomized to either the intervention or control arm as per this study protocol. If the patient is randomized to the control arm, the family physician will be informed that the referral for the NP would be scheduled for after study conclusion: 6 months after the date of referral. Family physicians will be given the additional opportunity of referring the patient to a community neurologist or a NP outside of the study if they feel that the patient cannot wait 6 months for MS specialized care. If the family physician opts for more urgent patient assessment, these patients will be excluded from being involved in the study.

Caregivers will be approached and invited to participate in the study, if the PwMS indicates a caregiver and contact information through their participant consent process. At the end of the informed consent, the PwMS will be asked whether they have a caregiver (with our definition for this study provided). If the participant answers ‘yes they have a caregiver’, they will be invited to provide the caregivers’ name, email address, and/or physical address. A separate informed consent will then be sent to the caregiver by email or by mail, outlining their involvement in the study and seeking their informed consent. Date of first enrolment was July 28, 2017, and recruitment was completed as of March 29, 2019.

